### Materials and instruments

#### Guidelines

Eleven PGs have been selected from the National Guidelines Clearinghouse http://www.guidelines.gov, CMA Infobase http://www.cma.ca/index.cfm/ci_id/54316/la_id/1.htm, and Guidelines International Network http://www.g-i-n.net/ directories for this study. One PG will serve as the practice PG for those assigned to the *tutorial + practice exercise *condition, and ten will serve as the test PGs in the study. Criteria for the PG search included: English-language PGs, PGs produced from 2002 onward, PGs with core text of 50 pages or less, and PGs targeting one of three clinical areas: cancer (n = 4), cardiovascular disease (n = 4), and critical care (n = 2). From the eligible candidates, and to choose a sample of ten test PGs, we selected PGs that reflected a range of quality on the Rigour of Development domain of AGREE II. Although we are not interested in the differences in PG topic as a primary factor, we want variability in clinical topic to make our findings more generalizeable.

#### AGREE II

The AGREE II consists of survey items and a user's manual.

#### Items

The AGREE II consists of 23 items grouped into six domains: scope and purpose, stakeholder involvement, rigour of development, clarity of presentation, applicability, and editorial independence. Items are answered using a seven-point response scale (strongly disagree-strongly agree). Standardized domain scores for PGs are calculated by summing scores across the appraisers and standardizing them as a percentage of the possible maximum score a PG can achieve per domain. This method enables the construction of a performance score profile permitting direct comparisons across the domains or items. The AGREE II concludes with two global measures answered using a seven-point scale: one targeting overall quality and the second targeting intention to use the PG.

#### User's manual

The AGREE II also comprises supporting documentation, referred to as the AGREE II user's manual. The user's manual provides details for each of the 23 items, including: explicit descriptors for the different levels on the seven-point rating scale; a description that defines each concept underlying the item and specific examples; direction on common places to look for the information and common terms or labels that represent to the concept(s); and guidance on how to rate the item, including specific criteria and considerations.

#### Learners' scale

In addition to the primary outcome of accuracy on the PG rating scale using AGREE II, secondary measures will also be collected: learner satisfaction, self-efficacy, mental effort, time-on-task, learner satisfaction, and self-efficacy with the training intervention will be measured using a seven-point scale. Mental effort will be measured on a seven-point scale, using self-report, and correlated with performance outcome to determine the cognitive efficiency metric [16]. Self-reported time-on-task related to the training time will be collected and checked against server logs. A time efficiency metric will also be determined, correlating time-on-task with performance outcome.

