### Sample Size

The primary analysis involves one-way analysis of variance (ANOVA) comparisons of the AGREE II performance score profiles of the three study group participants with the performance score profiles of AGREE II experts. This will be measured by the sum of squared deviations (SS) distance function. To avoid untenable assumptions regarding the relative size of the intermediate group mean, we simplify calculations by focusing on the power for testing differences in mean SS between the passive learning condition and either of the intervention groups, which represents a strong *a priori *comparison of the least and most effective interventions. Previous research has found the effect size of e-learning in comparison to no intervention to be large ranging from 1.13 to 1.50 [16-18]. Our intent is to estimate a more conservative effect size. Thus, with 20 participants per group, a one-sided test will have at least 80% power to detect an advantage of as little as ± 0.79 standard deviations for either of the intervention groups compared to the passive learning group. To account for potential missing data, we will include up to 25 participants per group for a total of 75 participants in the study.

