### Analyses

#### Performance -- distance function

Our primary outcome for performance will be a measure of distance in AGREE II item and domain rating profiles of the participants versus rating profiles of experts. The distance function will be calculated as the sum of the squared deviations (SS) between expert scores and participant's scores, summed over AGREE II items (SSi) and, alternatively, domains (SSd). Such a measure offers a precise and integrated summary of similarity over the whole profile of responses, and it provides a standard quadratic weighting of errors, consistent with other widely used measures of agreement, such as weighted kappa. Since the SS is typically skewed, we will use its square root in analysis. A series of one-way ANOVA tests will then be conducted to examine differences in distance function as a function of educational intervention.

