#### Learner's scales

A series of one-way ANOVA tests will be conducted to examine differences in participants' satisfaction, self-efficacy, cognitive effort, and time-on-task scores as a function of educational intervention.

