## Discussion

This project represents one of two initiatives of the AGREE A3 Consortium. We hope to complete this initiative in 2010. Our study findings will better inform KTE initiatives related to PG standards and evaluation, as well as the literature on instructional design and optimal training program design to balance learning and performance outcomes with time efficiency. In particular, our study will help determine the effectiveness and efficiency of practice exercises related to guideline review training, as well as learner satisfaction with web-based learning in this context.

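### The cognitive and time efficiency metrics are defined as correlations with performance, which cannot show which training arm is more efficient

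*Protocol article*

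**What the plan says.** Under Learners' scale, the article measures effort by self-report ("Mental effort will be measured on a seven-point scale, using self-report"). These ratings are then "correlated with performance outcome to determine the cognitive efficiency metric", with a citation (reference 16). The next metric is defined the same way, without a citation: "A time efficiency metric will also be determined, correlating time-on-task with performance outcome". No efficiency value per participant is described.

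Performance is defined under Performance -- distance function: "The distance function will be calculated as the sum of the squared deviations (SS) between expert scores and participant's scores". Its square root is analysed, so lower values are better.

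Under Learner's scales, one-way ANOVAs examine "differences in participants' satisfaction, self-efficacy, cognitive effort, and time-on-task scores as a function of educational intervention". Neither efficiency metric is listed there.

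Efficiency is a stated interest. The Introduction notes that practice and interactivity may cost learners time and make training less efficient, and says that this will be studied. The Discussion says that "our study will help determine the effectiveness and efficiency of practice exercises related to guideline review training", and that the findings will inform "optimal training program design to balance learning and performance outcomes with time efficiency".

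**The concern.** Whether practice exercises are efficient is a question about differences between arms: does one form of training give better performance for the effort or time spent? A correlation answers another question, namely whether learners who report more effort, or take longer, also score closer to or further from the experts. It carries no information about the arm means.

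If the metrics are reported as arm results, two arms that differ clearly in effort and performance can show the same efficiency. If they are pooled, a non-zero value may be read as a finding about learners when it comes only from the way the arms were built. Either way, the two measures that carry the name efficiency would not support the comparison the Discussion describes.

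**Working it through.** **Inputs from the protocol article**
- Sample Size: "with 20 participants per group, a one-sided test will have at least 80% power to detect an advantage of as little as ± 0.79" SD; up to 25 per group, 75 in total.
- Learners' scale: both metrics are correlations with performance.
- Tutorial with practice exercise: this arm gets the same tutorial and manual as the didactic arm, plus a practice appraisal, so its training is longer by design.

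**Assumptions not in the article**
- The effort shift is set to 0.79 SD, borrowed from the performance power statement.
- r, the within-arm correlation of distance with effort, is varied.
- The practice arm's extra time is set at 1 to 3 SD.
- Alpha is 0.05.

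**1. The plan's own figure.** With 20 per group, 0.79 SD and one-sided alpha 0.05, power is 80.3% by the normal approximation and 79.1% by the noncentral t with 38 df. The stated 80% is reproduced to within about a point. The point below does not depend on it.

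**2. Correlation within an arm.** Adding a constant to either variable leaves Pearson's r unchanged: corr(X + a, Y + b) = corr(X, Y). In 5,000 simulated trials with 25 per arm, both intervention arms were moved by 0.79 SD towards less distance and less effort, with r of 0, −0.3 and +0.3. The largest change in any within-arm correlation was 3 × 10⁻¹⁶, which is rounding error.

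**3. Effort correlation pooled over three equal arms.** If one arm, or two arms together, shift by 0.79 SD in both variables, the between-arm part of each variance and of the covariance is 0.79² × (1/3)(2/3) = 0.139. Hence pooled r = (r + 0.139)/1.139.

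| Within-arm r | Pooled, no shift | Pooled, with shift |
|---|---|---|
| 0 | 0 | 0.12 |
| −0.3 | −0.3 | −0.14 |
| +0.3 | +0.3 | 0.39 (0.38 simulated) |

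The pooled value does move. But (1/3)(2/3) is the same whichever arm shifts: at r = 0 the simulation gave 0.12 when only the control, only the tutorial or only the practice arm was better. The number does not identify the arm.

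**4. Time correlation pooled over arms, no within-arm relation.** Let the practice arm take k SD more time. The variance of time is 1 + k² × 2/9 (1.222 at k = 1; 3 at k = 3), and that of distance is 1.139.
- Only the practice arm improves by 0.79 SD: r = −0.79k(2/9)/√(1.139 × Var time), which is −0.15 at k = 1 and −0.28 at k = 3.
- Both intervention arms improve by 0.79 SD: r = −0.79k(1/9)/√(1.139 × Var time), which is −0.07 at k = 1 and −0.14 at k = 3.

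A correlation appears although time and performance are unrelated within every arm. Its size depends on the scenario.

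**5. A per-learner score under the same shift.** Take E = (z of performance − z of effort)/√2, with performance equal to minus the root distance. In within-arm SD units, the mean shift is (0.79 + 0.79)/√2 = 1.117 and the variance is (1 + 1 + 2r)/2 = 1 + r. The standardised shift is 1.117/√(1 + r).

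| r | Shift in E | Two-sided power, 20 per arm |
|---|---|---|
| +0.6 | 1.117/1.265 = 0.88 SD | 78% |
| +0.3 | 1.117/1.140 = 0.98 SD | 86% |
| −0.3 | 1.117/0.837 = 1.34 SD | 98% |

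In the simulated trials of step 2, the arm means of E were about −0.70 (control), +0.35 and +0.35. The score separates the arms where the within-arm correlation showed no change.

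**The case against.** The strongest reply is that the cognitive metric is named by reference. The cited source may define a standardised difference for each learner; the verb would then be loose wording, and the formula would belong in the full protocol. This cannot be settled here because the source is not shown. It would not clear the text: as written, both metrics are correlations, and the time metric cites nothing. If the source does define a per-learner score, the section misdescribes it and still needs correcting.

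The second reply largely stands. Distance, pass rate, effort and time-on-task are each compared between arms. An arm that does better with less effort would be seen in those results without any composite. What they do not give is a combined measure where the components conflict, such as better performance at the cost of more time, which is the trade-off the Introduction raises about practice.

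Three stronger readings are tempting and not supported:
- A reader might infer that the metrics cannot change at all. That is true only within an arm.
- A reader might infer a contradiction with the ANOVAs, because a correlation gives no value per learner. The plan lists no efficiency metric among its ANOVAs, so nothing is contradicted.
- A reader might infer that the sign is backwards, because distance is better when low. The section does not say how performance is signed in the metric, so this is a matter of labelling.

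**Conclusion.** The point holds for the two derived secondary metrics. Within an arm, the correlation is exactly unaffected by differences in means. Pooled, it is one trial-wide number that cannot rank the arms, and for time it is confounded with the design. Neither form can compare training efficiency between arms.

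A reader might go further and infer that the trial can say nothing about efficiency. The article does not support that, since performance, effort and time are compared separately. The primary analysis and the sample size are also untouched.

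The invariance is algebra and needs no assumption. The pooled values (about 0.12 for effort at r = 0; −0.07 to −0.28 for time) and the gain from a per-learner score (0.88 to 1.34 SD) are illustrations. They rest on an effort shift, a within-arm correlation and a time difference that the article does not give.

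**What to change.** Define both metrics per learner under Learners' scale:
- cognitive efficiency = (z of performance − z of mental effort)/√2;
- time efficiency = (z of performance − z of log time-on-task)/√2.

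Sign performance so that higher is better (minus the root distance), and standardise over all participants, not within arm. Add both scores to the one-way ANOVAs under Learner's scales, and report them beside the separate results for performance, effort and time. Report any correlation within arm only, as descriptive. If the cited source already defines such a score, change the wording to match it and define the time metric in parallel.

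The cost is a change of wording and a simple computation on data already planned. The drawback is that the score weights performance and effort (or time) equally, which is a choice and not a finding. That is why the components must be shown too.

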#### AGREE II experience scale

The Experience Scale, used originally with the AGREE Next Steps Project, will be modified and applied here. This scale asks participants about their experience in the PG enterprise (as developers, evaluators of PGs) and their experiences using the AGREE II tool (to facilitate development, reporting, and evaluation of PGs).

#### Expert norms

Expert norms will be compared to participants' AGREE II performance score profiles. Expert norms will be derived by members of the AGREE Next Steps research team who will appraise the PGs used in this study (n = 10). Mean standardized scores will be used to construct the expert performance score profiles.

#### Participants and procedures

Seventy-five participants will be recruited to participate in this study. Participants will reflect the range of potential PG and AGREE II users: clinicians, developers, and researchers, administrators, and policy makers. Because we found no differences in patterns of evaluation among user stakeholder group in the development work leading up to the release of the AGREE II [[10], http://www.agreetrust.org], we have not included stakeholders as a variable of interest.

Participants will be recruited from various sources, including: methodologists, clinicians, administrators, and policy makers involved in formal PG development programs; first authors of published PGs in the National Guideline Clearinghouse, CMA Infobase, and Guidelines International Network directories; professional directories and professional associations reflecting different stakeholder groups; clinical and health service researcher trainees; and the Guideline International Network community. A strong list of international collaborators will assist in our recruitment efforts. Candidate participants will be e-mailed a letter of invitation to participate in this study. After screening for their eligibility, participants will be randomly assigned by the research coordinator using a computer-generated randomization sequence to one of the three educational intervention groups. They will receive access to an individualized password-protected web-based study platform. There, participants will participate in the intervention to which they were assigned, complete an evaluation of one of the ten test PGs using the AGREE II, and complete a series the post-test Learner's Scales. Participants will be blinded to the other conditions.

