#### Test guideline ratings -- AGREE II scores

For exploratory purposes, a series of one-way ANOVA tests will be conducted to examine differences in participants' standardized AGREE II domain scores on the test PGs as a function of educational intervention.

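### The planned ANOVAs contain educational intervention only, although each participant rates one of ten test guidelines chosen to differ in quality, so between-guideline variation stays in the error term and precision is lost.

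*Protocol article*

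**What the plan says.** Under Participants and procedures in the protocol article, each participant receives the assigned training and will then "complete an evaluation of one of the ten test PGs using the AGREE II". Under Guidelines, the choice of the ten is described as deliberate: "we selected PGs that reflected a range of quality on the Rigour of Development domain of AGREE II". They also cover three clinical areas. That section adds that topic is not of interest as a primary factor.

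Under Performance -- distance function, the primary outcome is the square root of the summed squared deviations (root-SS) between the participant's and the experts' scores. The model is fixed as follows: "A series of one-way ANOVA tests will then be conducted to examine differences in distance function as a function of educational intervention". The exploratory section Test guideline ratings -- AGREE II scores uses the same one-way form for "differences in participants' standardized AGREE II domain scores on the test PGs as a function of educational intervention". The only covariate named anywhere is prior experience, and it is exploratory. No stated model contains the test PG.

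**The concern.** PG is a design variable here: it was chosen to vary, it is known for every participant, and each participant has exactly one value of it. It can move the distance score in three ways.

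- **Scale position.** On a 1-7 item, an expert norm of 4 allows at most 3 points of error, while a norm of 1 or 7 allows 6.
- **Shared norm error.** Everyone rating the same PG is compared with the same expert mean and shares whatever error it carries.
- **Difficulty.** Some PGs may simply be harder to rate as an expert would.

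A model with intervention alone puts all of this into residual error. With 20 to 25 raters per arm and power planned at the 80% threshold, that is a removable source of noise.

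The domain-score comparison is more exposed. It subtracts no expert score, and the PGs were selected to differ on one of the domains being compared.

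**Working it through.** **Inputs from the protocol article (Sample Size).** "with 20 participants per group", a difference of 0.79 SD, one-sided, at least 80% power. Recruitment is up to 25 per arm. There are three arms and ten test PGs.

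**Assumed, because not stated.** One-sided alpha is 0.05. The 0.79 is in units of the total SD. The share of root-SS variance due to PG, ρ, is varied.

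**1. The plan's own figure.** Normal approximation: 0.79 × √(20/2) − 1.645 = 2.498 − 1.645 = 0.853, and Φ(0.853) = 80.3%. The stated power reproduces. With the t distribution and the error pooled over three arms (60 − 3 = 57 df), it is 79.5%. This is the baseline below.

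**2. Adding PG with balanced assignment.** The residual SD becomes √(1 − ρ) and the residual df 60 − 10 − 2 = 48. Power is from the noncentral t with noncentrality [0.79/√(1 − ρ)] × √10.

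| Assumed PG share ρ | 0.79/√(1 − ρ) | One-sided power with PG in the model |
|---|---|---|
| 0 | 0.790 | 79.3% |
| 2% | 0.798 | 80.0% |
| 6% | 0.815 | 81.5% |
| 10% | 0.833 | 83% |
| 20% | 0.883 | 87% |
| 30% | 0.944 | 90% |

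The first row is the price if PG has no effect: 79.5% − 79.3% = 0.2 points.

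**3. Where the 2-6% comes from.** A simple simulation let PGs differ only in scale position (mean norms 2.5-5.5, item SD 1-2, rater bias SD 0.6, item error SD 1.3, shrinkage to mid-scale 0-0.4). It gave a PG share of 2-6% for root-SS and 42-71% for mean item scores. A repeat with ratings rounded to whole points gave 0-4% and 41-71%. All inputs are assumed. Differences in difficulty and shared norm error would add to the root-SS share.

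**4. Chance imbalance under random assignment.** The SD of the PG contribution to a two-arm difference is √(2ρ/20 × 0.9). That is 0.04 and 0.07 SD at ρ = 2% and 6%, and 0.09, 0.13 and 0.16 SD at 10%, 20% and 30%.

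**5. Behaviour of the one-way test.** Simulation with 3 arms of 20, ten PGs and 5,000 runs:

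- *PGs assigned at random:* no average bias; type I error 0.048-0.055; power about 79-81% whatever ρ is.
- *PGs balanced, not modelled:* type I error 0.047, 0.040 and 0.023 at ρ = 10%, 20% and 30%, and power 81%, 82% and 84%. With PG in the model, power is 83%, 87% and 90%. Balance alone therefore recovers only part of the gain.

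**6. Fixed PG effects without balance.** At ρ = 0 and 20 per arm, one-sided power falls to about 73%, a loss of 6-7 points. Break-even is near ρ = 20%.

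**7. Domain scores.** If the share were 42-71%, the one-way error SD would be inflated by 1/√0.58 = 1.3 to 1/√0.29 = 1.9.

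**The case against.** Much of the case on the other side stands.

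- **Confounding.** A reader might infer that PG differences confound the arms. The documents do not support that. Participants are randomised to arms, and nothing says that the PG depends on arm. With PG assigned independently of arm, imbalance is random error that the one-way test already reflects. How PGs are allotted is a detail that an article may leave to the full protocol, so its absence is no fault.
- **Size.** A reader might take the between-PG variance as known to be large. It is not given. The primary outcome is a distance from expert profiles, which removes much of the quality level, and the PGs were selected on one domain of six. If scale position is all that differs, the gain is about 0.5-2 points.
- **Underpowering.** A two-sided calculation gives 69% without PG, and a reader might blame PG variation for that. The plan is one-sided, so the gap is about sidedness and not about PGs.
- **No cost.** A reader might think that adjustment is free. It nearly is under balance, but not with fixed effects under unbalanced assignment.
- **Exploratory status.** The analysis hit hardest is labelled exploratory.

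What does not stand is that lack of interest in topic justifies the one-way model. It explains not testing PG effects; it is no reason to leave a designed source of variation in the error term. Nor is this a detail left to another document, because the article names the model.

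**Conclusion.** The point holds as one of efficiency, not validity. The stated models omit a factor that the design itself introduces. Under random assignment the primary test is unbiased and keeps its level, and what is lost is precision. Under balanced assignment it is conservative.

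For the primary outcome, the combined gain from balance and the PG term is about 0.5-2 points of one-sided power at a share of 2-6%, and about 3.5, 7 and 11 points at 10%, 20% and 30%. These figures rest on an assumed share, a one-sided 5% level and 0.79 in total-SD units. If 0.79 were meant in within-PG units, the one-way power by normal approximation, Φ(0.79 × √(1 − ρ) × √10 − 1.645), would be 77%, 72% and 67% at those three shares.

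The exploratory domain-score comparison is the most affected in direction. Its size also rests on assumed inputs.

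**What to change.** 1. Balance the test PGs across arms, if the full protocol does not already do so, by assigning them at random in sets of ten within each arm. That gives two uses per PG per arm at 20 and two or three at 25.
2. Replace the one-way ANOVAs in Performance -- distance function and in Test guideline ratings -- AGREE II scores by a model with intervention plus test PG.
3. Tie the form of the PG term to the assignment: a fixed block when assignment is balanced; a random intercept if it is unbalanced or if dropout (the plan allows for 25 falling to 20 per arm) erodes the balance. Settle this rule before the data are seen.

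The cost is an assignment list, a sentence of analysis wording and nine degrees of freedom. Under balance that is less than one point of power if PG has no effect. Fixed PG effects without balance would cost about 6-7 points in that case, which is why the two parts of the change belong together.
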